### Waitlist (WL) control

Individuals randomized to WL will continue in their usual care. After they complete their 13-week and 6-month assessments, which are identical to the SMART group assessments, WL individuals will begin participating in the SMART intervention for the next 12 weeks. Once the WL individuals begin participating in SMART, they will have research assessments at 13 weeks, 6 months, and 12 months after beginning SMART.

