### Outcomes and analysis

Table 2 outlines study procedures. In addition to demographic and clinical information (age, gender, ethnicity, self-reported cumulative medical illness [19, 20]), health literacy will be assessed [21] to detect persons with limited or marginal health literacy. For both the SMART and the WL groups, research assessments will be done at screening (to establish study eligibility), at baseline, and at 13 weeks, 6 months, 12 months, and 18 months after randomization. Members of the waitlist will also be assessed 13 weeks after starting the SMART intervention. All assessments are suitable for remote administration either by phone or using REDCap (Research Electronic Data Capture), a secure Web application for building and managing online surveys and databases [22]. REDCap will be used for secure data entry and storage.

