#### Primary outcome

The primary outcome will be the proportion of individuals with reduction in their total number of NHEs in the prior 6 months at baseline compared to week 24 of the trial. The prior SMART study had a nonstandard distribution of NHEs and a high proportion of subjects with no NHEs at 6-month follow-up, so a longitudinal binary mixed model (no NHE or at least one NHE) will be used as opposed to a count regression model [10]. The second primary outcome will be the change in NHE counts in the 6 months prior to baseline compared to week 24 of the trial. NHEs are defined as seizures, emergency department visits, hospitalizations, and self-harm attempts. NHE reporting will be via self-report with corroboration by EHR documentation and report of family/support system informants whenever possible. In addition to total NHEs, we will assess NHEs in each category, including seizure frequency and length of stay in days for hospitalization NHEs. These domains (total number of NHEs, seizure frequency, length of hospital stay) will be assessed for differences between the two groups looking at mean and median values. A type I error rate of 0.05 will be considered significant.

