#### Secondary/additional outcomes

Additional assessments will include evaluation of depressive symptoms using the PHQ-9, a widely used and validated self-rated depression scale [23]. Functional health status will be assessed using the 36-Item Short Form Survey (SF-36), a multi-purpose, short-form health survey that yields two psychometrically based components: a physical component summary and a mental component summary, which has proven useful for comparing the relative burden of diseases [24]. Epilepsy control will be assessed via self-reported seizure frequency. Quality of life will be assessed with the Quality of Life in Epilepsy (QOLIE-31) self-administered questionnaire which comprises 7 components including seizure worry, overall quality of life, emotional well-being, energy-fatigue, cognitive functioning, medication effect, and social function [25, 26]. These domains (score on PHQ-9, score on SF-36, self-reported seizure frequency, and score on QOLIE-31) will be assessed for differences between the two groups looking at mean and median values at baseline and 13 and 24 weeks of trial and change over time from baseline to 24 weeks of trial. A type I error rate of 0.05 will be considered significant.

Other factors assessed in the trial include epilepsy self-management competency, self-efficacy, social support, and stigma. Self-efficacy will be measured with an Epilepsy Self-Efficacy Scale (ESES) 2000 version. The ESES was developed based on Bandura’s conceptualization of self-efficacy to assess a person’s confidence in his or her ability to use self-management strategies. Previous studies show acceptable construct validity and high test-retest reliability in the ESES [27–29]. Social support will be measured with the Multidimensional Scale of Perceived Social Support (MSPSS), a 12-item scale that measures an individual’s perception of social support provided by family and friends, as well as satisfaction with that support [30]. Stigma for epilepsy will be measured using the 24-item Stigma Scale of Epilepsy (SSE) developed by the Demonstration Project on Epilepsy as part of the WHO/ILAE/IBE Global Campaign against Epilepsy [31, 32]. The SSE is a validated, versatile, and sensitive instrument which has been used mainly in resource-poor settings to study stigma in epilepsy.

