### Data analysis

Descriptive analyses will compare the individuals assigned to SMART or WL using Student’s *T*-test, Fisher’s exact test, and non-parametric tests when appropriate. The primary outcome is whether there is a difference in the proportion of individuals with reductions in the total number of NHEs in the prior 6 months, at baseline, and at follow-up (6 months after randomization) between SMART and WL, compared using a Fisher’s exact test. We will also test for the difference in NHE counts between baseline and follow-up using a non-parametric Wilcoxon-Mann-Whitney test (the distribution of this measure is expected to be non-normal based on our prior experience). Exploratory longitudinal mixed models with a subject-level random effect will be conducted to investigate a binary variable of no NHEs versus at least one NHE and for a count measure of total NHEs from baseline to 10 and 24 weeks. Explanatory variables will include study site, age, gender, race/ethnicity, number of seizure medications, rural/urban continuum status, and attendance or deviations from the study protocol. Analysis will be performed for the intention-to-treat population (all participants enrolled to receive the SMART trial), for the safety population (all participants who received any portion of the SMART intervention), and for the per-protocol population (all participants who completed the SMART intervention). There will be a delay between randomization and baseline assessments for individuals enrolled for both the SMART trial and the waitlist, which may vary based on the recruitment time required for cohorts and the number of cohorts that can be accommodated at one time. Every effort will be made to insure steady recruitment and sufficient numbers of cohorts to accommodate those recruited. In addition, the specific cohorts will be able to be identified for analysis, and if we find marked variability between the cohorts or the delay in starting the intervention, this will be addressed by the data monitoring committee.

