The 12-month and 18-month measurements of NHEs will be compared to baseline and 6-month measurements as well. We will also examine change-over-time in the secondary outcomes using parametric and/or non-parametric tests as deemed appropriate for each measure. NHE measurements will reflect the preceding 6-month time period, except for the 13-week time period. The 13-week NHE measurement will reflect the time period following baseline (when individuals participating in SMART will be having their “intensive” group sessions), and it will be used to assess for within-subject differences from baseline to 13-week and 13-week to 6-month time periods. Note that the 13-week to 6-month NHE count will be derived by subtracting the measurement taken at 13 weeks from the one taken at 6 months. This will allow for a greater understanding of the time course for when the expected reductions occur in the SMART group, which we expect to mostly occur after the “intensive” 8 group sessions have ended. A secondary analysis of NHEs will include a comparison of hospital and emergency department visits. A 2-sided type I error rate of 5% will be considered significant.

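### The exploratory NHE models name a week-10 time point that no described visit supplies, and the 6-month endpoint has two labels and no single time origin

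*Protocol article*

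**What the plan says.** All places are in the protocol article.

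- **Data analysis, first paragraph.** "Exploratory longitudinal mixed models with a subject-level random effect will be conducted" for a binary NHE variable and "for a count measure of total NHEs from baseline to 10 and 24 weeks". The same paragraph places the primary follow-up six months after randomization. It also says that baseline assessments will follow randomization after a delay that may vary with cohort recruitment.
- **Outcomes and analysis.** Both arms are assessed "at screening (to establish study eligibility), at baseline, and at 13 weeks, 6 months, 12 months, and 18 months after randomization".
- **Waitlist (WL) control.** Waitlist participants start SMART "After they complete their 13-week and 6-month assessments, which are identical to the SMART group assessments".
- **Primary outcome.** The comparison is of "NHEs in the prior 6 months at baseline compared to week 24 of the trial".
- **Secondary/additional outcomes.** Scores are compared "at baseline and 13 and 24 weeks of trial".
- **Data analysis, second paragraph.** "NHE measurements will reflect the preceding 6-month time period, except for the 13-week time period". The 13-week count covers the time since baseline. The count for 13 weeks to 6 months is obtained by subtracting the 13-week count from the 6-month count.

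**The concern.** There are two separate timing problems.

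First, the mixed models are given a time point at which nothing is scheduled to be measured. An analyst who follows the text has no week-10 count to enter and must decide alone what was meant.

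Second, the visit that carries the primary endpoint has two nominal times, and its origin is not fixed. Visits are timed from randomization, the 13-week NHE window starts at baseline, and the two dates differ by a variable delay. This matters because the 6-month NHE count is defined by a fixed look-back and not by a start date. If the look-back opens before the baseline assessment, events from before baseline are counted as follow-up, and the same events also sit in the baseline count. The subtraction that yields the second-period count is valid only if the 13-week and 6-month windows start on the same day. Participants are recruited because of a recent NHE (Setting and recruitment), so the weeks before baseline cannot be assumed free of events. A single such event also moves a participant from no NHE to at least one in the binary model.

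**Working it through.** **1. Week 10 against the schedule.** Times named within the first six months after baseline:

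| Section | Times |
|---|---|
| Outcomes and analysis | 13 weeks, 6 months |
| Waitlist (WL) control | 13 weeks, 6 months |
| Secondary/additional outcomes | 13 weeks, 24 weeks |
| Data analysis, second paragraph (NHE windows) | 13 weeks, 6 months |
| Data analysis, first paragraph (mixed models) | 10 weeks, 24 weeks |

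Only the last row has week 10. It lies 13 − 10 = 3 weeks before the nearest visit. The Experimental intervention section lets the group sessions run for 10 to 12 weeks, so week 10 does not reliably mark their end either.

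**2. Week 24 against 6 months.**
- 24 weeks = 24 × 7 = 168 days.
- 6 months = 6 × 365.25/12 = 182.6 days, or 182.6/7 = 26.1 weeks.
- Gap = 182.6 − 168 = 14.6 days, and 14.6/182.6 = 8.0%.
- 13 weeks = 91 days, and 91/182.6 = 49.8%. The 13-week visit is therefore the midpoint of a 26-week half-year.
- The two programme stages in the Phase 2 section add to 12 + 12 = 24 weeks, a likely source of the other label.

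**3. A visit held literally at week 24 from baseline**, with a look-back of about 26 weeks:
- The window opens at week 24 − 26 = −2.
- Pre-baseline share of the follow-up window: 2/26 = 7.7%, about 8%.
- Subtracting the 13-week count leaves 26 − 13 = 13 weeks of counted time. That is 24 − 13 = 11 weeks after the 13-week visit plus 2 weeks before baseline, so the pre-baseline share is 2/13 = 15.4%, about 15%.

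**4. A visit at 6 months from randomization**, with baseline d weeks after randomization:
- The look-back opens at randomization, so d weeks of the window precede baseline, a share of d/26.
- The article gives no value for d. For assumed delays of 1, 2 and 4 weeks the shares are 1/26 = 3.8%, 2/26 = 7.7% and 4/26 = 15.4%. With d = 0 the problem disappears.
- Setting the visit at 26 weeks does not help while the origin remains randomization.

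**5. What does not move.** Attrition reproduces: 160 × 0.80 = 128. The 86% power for Fisher's exact test cannot be reproduced, because the article does not give the assumed proportions. By exact enumeration at 64 per arm, that power needs an absolute difference of about 0.22 to 0.285 for assumed waitlist proportions of 0.2 to 0.7. None of these figures depends on visit timing, and neither primary test uses a week-10 measurement.

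**The case against.** The strongest reply is that these are slips of wording with an obvious meaning. The models are called exploratory, and every other description of the schedule points to 13 weeks. The article uses week 24 and 6 months for the same primary endpoint, and no separate week-24 visit is listed. The visit schedule table is also not visible. Most of this stands, and it limits the point in three ways.

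- A reader might infer that week 24 is a different visit from the 6-month one. The documents do not support that. It is most likely a loose label for one visit, and the figures in step 3 apply only if the label is taken literally.
- A reader might infer that entering the 13-week count as week 10 would create a false fall in the event rate. That needs a rate model with nominal weeks as exposure time. The article states no offset, no rate and no continuous time. With visit as a category the label changes no estimate, and in a log-rate model an artefact common to both arms cancels from the comparison of SMART with waitlist. The planned time-course analysis is a separate within-subject comparison that uses 13 weeks and 6 months, not week 10.
- A reader might infer that the week-10 error undermines the primary tests or the power. It does not, for the reason in step 5.

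The reply does not remove the contradiction within the analysis text, nor the open question of where the 6-month look-back begins. The second bears on the count used for the primary endpoint. The Primary outcome section also names a binary mixed model without calling it exploratory. If that reading prevailed, the week-10 error would weigh more, but that conflict is a separate matter.

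**Conclusion.** The point holds, at minor to moderate severity. The week-10 time point contradicts the described schedule and the NHE window definitions, so as written the exploratory models have no scheduled measurement there. This rests on the text sections, which agree with one another; the schedule table could not be checked.

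The two labels for the primary follow-up differ by about 2 weeks. Under a literal week-24 visit with a six-month look-back, about 8% of the follow-up window and about 15% of the derived second period would precede baseline. Under timing from randomization, the pre-baseline time equals the delay to baseline, whose length is not given. These are alternative ways of reading the text, and neither is shown to be what the trial will do. No primary result is shown to be wrong.

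**What to change.** 1. In the first paragraph of Data analysis, replace the 10-week and 24-week time points with the 13-week and 6-month assessments.
2. Use one nominal time and one time origin for the 6-month visit in Outcomes and analysis, Primary outcome, Secondary/additional outcomes and Data analysis.
3. Define the 13-week and 6-month follow-up NHE counts as events since the baseline assessment date. Both windows then start on the same day, the subtraction is valid, and no event is counted both at baseline and at follow-up.
4. Use actual assessment dates for interval length in any count model.

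The cost is wording and minor data handling, with no added visits and no change to the sample size. One consequence should be stated with the change. If visits stay timed from randomization, or are held at week 24, a count since baseline covers less than six months while the baseline count covers a full six. Timing the visit at six months from the baseline assessment keeps the two windows equal.

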### Experimental intervention

The SMART curriculum is divided into 2 steps. Step 1 consists of eight group format 45–60-min sessions with up to 10 participants per group, which will be collaboratively delivered by a nurse educator and a peer educator. The intervention will be delivered in a Web-based format emphasizing interactive discussion with a secure videoconferencing system. Participants will be able to log on and interact via audio and/or video. Telephone call-in will be available for those who do not have Internet access. Patients will receive e-mail and phone call reminders of sessions, and make-up sessions will be available. The initial group-session portion of SMART will be completed over 10–12 weeks (Table 1). Following the step 1 group sessions, step 2 consists of 3 brief (no more than 15 min) monthly Web-based or telephone maintenance sessions conducted by the nurse educator. Telephone sessions will address ongoing issues of epilepsy self-management including treatment adherence. Additionally, the nurse will serve as a facilitator of linkage between the individual’s epilepsy care clinicians by providing SMART program status updates to providers.

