### Feasibility and fidelity

Attendance for each SMART session will be recorded. Acceptability will be assessed at the end of each 12-session group series with a brief self-rated survey. Following Fraser [18], fidelity to the SMART intervention will be assessed quantitatively and qualitatively. Non-interventionist research staff will monitor and assess at least 25% of group sessions, with each fidelity dimension being rated on a 1–10 scale.

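### Attendance and protocol deviations, both arising after randomization, are listed as explanatory variables in the mixed models of negative health events, where they can distort the SMART-versus-waitlist effect

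*Protocol article*

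**What the plan says.** All references are to the protocol article.

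- **Models.** Data analysis introduces them thus: "Exploratory longitudinal mixed models with a subject-level random effect will be conducted to investigate a binary variable of no NHEs" against at least one, and also "for a count measure of total NHEs from baseline to 10 and 24 weeks". The window is therefore the randomized comparison period.
- **Covariates.** The next sentence reads: "Explanatory variables will include study site, age, gender, race/ethnicity, number of seizure medications, rural/urban continuum status, and attendance or deviations from the study protocol".
- **Meaning of attendance.** Feasibility and fidelity says: "Attendance for each SMART session will be recorded". Experimental intervention gives the number of group sessions: "Step 1 consists of eight group format 45–60-min sessions with up to 10 participants per group".
- **Waitlist.** Under Waitlist (WL) control, these participants remain in usual care and start SMART only once their 13-week and 6-month assessments are done.
- **Primary tests.** The first primary outcome is the proportion with a reduction in NHEs, "between SMART and WL, compared using a Fisher’s exact test". For the second: "We will also test for the difference in NHE counts between baseline and follow-up using a non-parametric Wilcoxon-Mann-Whitney test". Neither has covariates.
- **The binary model's second appearance.** Under Primary outcome, "a longitudinal binary mixed model (no NHE or at least one NHE) will be used as opposed to a count regression model". The word exploratory is absent there.

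**The concern.** A covariate in a comparison of randomized arms should be unaffected by allocation. Session attendance is a direct result of allocation and part of the route by which SMART is meant to work. Conditioning on it removes from the arm effect whatever benefit passes through the sessions, and it compares SMART participants of a given attendance with controls who had no opportunity to attend. If attendance also reflects prognosis, the adjusted arm effect can be wrong in either direction.

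Deviations from protocol also happen after randomization, and only the SMART arm has sessions from which to deviate during the comparison period. Near-collinearity with arm is a problem of attendance only, because deviations can occur in both arms.

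At stake is whether the covariate-adjusted NHE results can be read as estimates of the randomized effect, and whether they could seem to contradict the primary tests for purely technical reasons.

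**Working it through.** **1. Is attendance absent in controls over the modelled window?** The models end at 24 weeks. Waitlist participants start SMART after the 6-month assessment. Attendance is therefore zero by design, or undefined, for all of them. If it were coded as missing, a complete-case fit would lose every control. The article does not state the coding.

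**2. Does any text confine attendance to SMART participants?** No. The covariate sentence refers to the mixed models as a whole.

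**3. Loss of precision in the simplest case.** Take a linear model at one time point with arm and attendance, 1:1 allocation and attendance zero in controls. Let SMART attendance have mean m and standard deviation s.

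- Between-arm variance of attendance: (m/2)²
- Average within-arm variance: s²/2
- R² = (m/2)² / [(m/2)² + s²/2]
- Variance inflation (VIF) = 1/(1 − R²); the standard error grows by √VIF

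The article gives neither m nor s. Assumed range: m from 5 to 6 of 8 sessions, s from 2 to 2.5.

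| m | s | R² | VIF | √VIF |
|---|---|---|---|---|
| 6 | 2 | 9/(9 + 2) = 0.818 | 5.5 | 2.3 |
| 5 | 2.5 | 6.25/(6.25 + 3.125) = 0.667 | 3.0 | 1.7 |

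**4. Direction of bias in the same simple model.** A simulation used 64 per arm (160 × 0.80 = 128 evaluable, as in Sample size calculations), a standardized outcome, mean attendance of about 6 of 8 and 3,000 runs. Where an effect was present it was about 0.55 SD, negative meaning benefit.

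| Assumed truth | Arm alone | Arm + attendance |
|---|---|---|
| Benefit proportional to sessions, attendance unrelated to prognosis | estimate −0.55, rejection 87% | 0.00, 5% |
| Constant benefit, unrelated to attendance | −0.55 (SE 0.18), 86% | −0.55 (SE 0.43), 25% |
| No effect, better-prognosis patients attend more | 0.00, 5% | +1.17, 70% |

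The inputs are assumptions. The rows show that the effect can be masked, blurred or falsely created; they are not forecasts for this trial.

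**5. Does the longitudinal form remove the problem?** Partly, and only for some specifications. If baseline is one of the responses and the treatment effect is the arm-by-time term, an attendance main effect that is constant over time competes with the arm main effect, that is, with the baseline difference. In an illustrative three-time-point simulation with benefit fully proportional to attendance, the week-24 arm-by-time estimate was −0.72 (SE 0.18) in a linear model and −0.70 (SE 0.15) in a count model, in each case both with and without attendance. Harm returns if arm enters without a time interaction, or if attendance also interacts with time.

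The binary model is less well protected. Entry requires an NHE in the preceding 6 months (Setting and recruitment), so its baseline response is at least one NHE for essentially everyone. Little is then left at baseline to separate arm from attendance.

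**The case against.** The strongest reply has four parts.

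- **The models are exploratory.** Data analysis says so, and both primary tests, on which the power statements rest, are unadjusted. This stands. A reader might infer that the trial's primary result is compromised; the documents do not support that. It is only softened by the Primary outcome section, which describes the binary model without that label.
- **The model form is not fixed.** The list does not name arm and does not say that all terms enter together. The same section also plans analyses of those who received or completed SMART, where attendance would be a natural dose variable. This stands as far as it goes. A reader might infer that the plan's models certainly absorb the treatment effect, or that a 1.7- to 2.3-fold standard error is to be expected; neither follows, as step 5 of the working shows. Still, these models follow directly on SMART-versus-waitlist tests, the trial's hypothesis is that comparison, and nothing reserves attendance for SMART recipients.
- **It can wait for the analysis plan.** That would answer an omission. Here the article positively names the variables that will be included.
- **Baseline NHE burden is the covariate really missing.** A reader might infer this from the list. It does not hold: baseline NHEs already belong to the modelled response, so the count would stand on both sides of the model.

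**Conclusion.** The point holds in a limited form. The article lists two post-randomization variables for mixed models that span the randomized period, and one of them cannot take a meaningful value in the waitlist arm. In a SMART-versus-waitlist model this can bias the arm effect or make it imprecise.

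The size is not determined by the document. The 1.7- to 2.3-fold standard error rests on assumed attendance and a single-time-point linear model; an arm-by-time specification could leave the linear and count results almost untouched. For deviations the objection is only that they follow randomization and can mean different things in the two arms; no definition is given, so no size can be attached.

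The unadjusted primary tests are unaffected. The matter is moderate and worth correcting, because it concerns the adjusted NHE models and one of them is also described under Primary outcome.

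**What to change.** In Data analysis, restrict the between-arm mixed models to arm, time and the listed pre-randomization covariates: site, age, gender, race/ethnicity, number of seizure medications and rural/urban status. State that arm is in the model and which term carries the treatment effect.

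Move attendance and deviations to a separate analysis, either a dose-response description within the SMART arm or a causal adherence analysis such as a complier average causal effect, labelled exploratory and non-randomized. Do not add baseline NHE count as a covariate while baseline NHEs are part of the response. Make the Primary outcome section agree with Data analysis on the exploratory status of the binary model.

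The cost is an edit of a sentence or two. No further data are needed, since attendance is already recorded, and sample size and primary tests do not change.

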### Community Advisory Board (CAB)

Building upon strong existing partnerships between members of the study team and epilepsy/neurological care partners across the states of Iowa and Ohio, the study team will obtain input from relevant community stakeholders to develop an a priori recruitment and retention strategy intended to maximize enrollment of typically hard-to-reach individuals with epilepsy from underserved and rural communities. The CAB will be composed of up to 16 individuals, including individuals with epilepsy, epilepsy specialists, clinicians, and administrators who practice in rural or underserved communities, and representatives from the Epilepsy Association/Epilepsy Foundation.

There will be 3 video-conference calls prior to the RCT. In the first call, CAB members will review the SMART curriculum and identify potential barriers to recruitment and retention. In the second meeting, CAB members will review the list of barriers and suggest solutions and strategies for reaching people with epilepsy who may not be initially help-seeking and discuss potential methods of retaining these individuals in the program once they are recruited. In the third CAB meeting, the list of strategies will be finalized, and the investigators will obtain input on how these strategies might be best operationalized.

### Phase 2

Phase 2 is a prospective 6-month comparative trial of SMART vs. WL in 160 individuals with epilepsy and a recent NHE. Participants will be randomly assigned (1:1 basis) to receive either SMART (*N* = 80) or WL (*N* = 80) using a computer-generated random number generator created in REDCap during the enrollment process. This is a simple randomization scheme together with permuted block randomization to insure similar treatment and waitlist group sizes. This randomization scheme is unavailable to study staff who enroll participants and assign to treatment or waitlist groups. The participants and nurse and peer educators are not blinded, due to the nature of the intervention. However, the data analysts have no interaction with participants or the nurse or peer educators. The investigators will conduct 8–10 separate and sequential SMART groups with up to 10 individuals in each group. SMART will consist of two main components: a 12-week remotely accessed “intensive” group format stage and a 12-week remotely accessed Web/telephone follow-up stage.

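### The three analysis sets are defined only by SMART participation, so the safety and per-protocol sets hold no concurrent waitlist controls and the intention-to-treat wording is ambiguous

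*Protocol article*

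**What the plan says.** Three sets are named in the Data analysis section of the protocol article.

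- ITT: "Analysis will be performed for the intention-to-treat population (all participants enrolled to receive the SMART trial".
- Safety: "for the safety population (all participants who received any portion of the SMART intervention".
- Per-protocol: "for the per-protocol population (all participants who completed the SMART intervention".

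The next sentence of that section speaks of "individuals enrolled for both the SMART trial and the waitlist", which makes the SMART trial the counterpart of the waitlist. The same section sets the primary contrast as one "between SMART and WL, compared using a Fisher’s exact test". The Phase 2 section fixes allocation: "Participants will be randomly assigned (1:1 basis) to receive either SMART (*N* = 80) or WL (*N* = 80". Under Waitlist (WL) control, the WL arm stays in usual care through its 13-week and 6-month assessments, and only then "WL individuals will begin participating in the SMART intervention for the next 12 weeks". The sample size section assumes 20% attrition, leaving 128 participants over both arms, and 86% power for a two-sample Fisher's exact test.

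**The concern.** Each definition turns on what a person does with SMART, and none says where a WL participant belongs. Two of the sets depend on receiving or completing an intervention that WL cannot have before the primary endpoint. The control side of any 6-month comparison in those sets is therefore empty, or has to be filled by a rule the article does not give. If that rule is chosen once the data are in hand, the choice can move the result.

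The ITT set matters most because it should carry the primary conclusion. Its wording does not say that everyone randomized is counted in the assigned arm. This is a practical question in this trial: the Data analysis section expects a variable delay between randomization and baseline while cohorts fill, and people can be lost in that interval. Nor does the article say which of the three sets supports the primary conclusion.

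**Working it through.** **1. The plan's own figure.** Randomized: 80 + 80 = 160. After 20% attrition: 160 × (1 − 0.20) = 128, or 64 per arm. This agrees with the sample size section and shows that the primary test is planned on both arms.

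**2. Who can be in each set at 6 months, as written.**

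| Set | Condition | SMART | WL |
|---|---|---|---|
| ITT, literal reading | enrolled to receive SMART | 80 | 0 |
| ITT, as step 1 requires | all randomized | 80 | 80 |
| Safety | received any SMART | at most 80 | 0 |
| Per-protocol | completed SMART | at most 80 | 0 |

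The zeros for safety and per-protocol follow from the WL section alone. With no WL participants, a two-sample Fisher's test cannot be run.

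**3. Two ways to supply controls.**

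(a) Admit WL participants who start or finish SMART after month 6. Control membership then depends on behaviour after the endpoint being compared.

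(b) Compare SMART completers with all WL. Selection then acts in one arm only.

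**4. Illustration of (b) with no treatment effect.** Assumptions, not document figures: 50% of each arm improves; in the SMART arm, completion is 85% among improvers and 65% among the rest.

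- Completion overall: 0.5 × 0.85 + 0.5 × 0.65 = 0.75, so 64 × 0.75 = 48 completers.
- Improved among completers: 0.425 / 0.75 = 56.7%, against 50% on WL, a difference of +6.7 points.
- With the two rates swapped: 0.325 / 0.75 = 43.3% against 50%, a difference of −6.7 points.
- Exact two-sided Fisher rejection rate, 48 versus 64, is 8.3% in either case. The randomized comparison of 64 versus 64 at 50% gives 3.0%.

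**5. Range.** If completers do better than non-completers by a gap g, with completion share c and 50% improving overall, the spurious difference is (1 − c) × g. For c from 60% to 80% and g from 10 to 30 points, it runs from 0.20 × 10 = 2 points to 0.40 × 30 = 12 points. The Fisher rejection rate runs from 4% to 19%. A gap of the opposite sign reverses the difference.

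**6. Scale.** The article gives no pair of proportions behind the 86% power. Inverting the exact test at 64 per arm gives a difference of about 25 to 28 points for assumed WL proportions of 30% to 60% (for example 50% versus 76.7%). Against that, 6.7 points is about a quarter (6.7 / 26.7 = 0.25).

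**The case against.** The ITT phrase is probably loose wording, since nobody is enrolled to receive a trial. The 1:1 allocation, the SMART-versus-WL primary test and the two-arm power calculation all point to an intention to analyse everyone. That largely stands. A reader might infer that the plan discards its controls or gives up the protection of randomization, and the article as a whole does not support that. But the very next sentence sets the SMART trial against the waitlist, so the phrase needs correcting whichever meaning was intended.

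Defining a safety set by exposure is common practice. Hospitalization and self-harm are components of the negative health event outcome, which the Primary outcome section already assesses by category and between groups. This stands too: those comparisons do not depend on the safety set and are not lost. What remains is that the set named for safety has no control arm over the first 6 months.

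A reader might also infer that the per-protocol result must favour SMART. The article gives no completion rates by outcome and never says that completers will be compared with all WL. Step 4 shows that the sign turns on an assumption. Exposure-defined sets could also serve the within-subject or 12- and 18-month analyses. The article does not exclude that use, but does not limit the sets to it either.

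Finally, these definitions are not detail left to an analysis plan. The article states them, and in a form that does not fit its own primary comparison.

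**Conclusion.** The point holds as a defect in stated definitions. For the safety and per-protocol sets it is certain: at 6 months, as written, neither can contain a concurrent control. For ITT it is an ambiguity that conflicts, on a literal reading, with the two-arm test and the total of 128; the intended meaning is probably all participants.

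The consequence for a per-protocol result cannot be sized from the article. The ±6.7 points, the 2 to 12 points and the rejection rates of 4% to 19% all rest on assumed completion and prognosis, and the direction is unknown. The definitional fault does not depend on these figures.

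**What to change.** Reword the definitions in the Data analysis section.

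- **ITT:** all randomized participants in both arms, analysed as randomized whatever their attendance, and named as the basis of the primary conclusion.
- **Safety:** 6-month comparisons include WL participants, classified by treatment received in that period. Say how their data are handled once they start SMART.
- **Per-protocol:** a separate rule for each arm, using only events up to the 6-month assessment, labelled supportive. Alternatively, report completers descriptively with no between-arm test.
- **Optional alternative:** a complier-average estimate with randomization as the instrument. WL has no planned access to SMART before 6 months, so non-compliance should be one-sided. The estimate also needs the assumption that assignment acts on the outcome only through SMART, which should be stated and defended.

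The cost is wording and a little extra analysis. Sample size, visits and data collection do not change.
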